### Statistical analysis

2.7

We will compare the results of the statistical analyses between the LA and the SLA groups. The data will be expressed as frequencies, percentages or mean ± standard deviation and analyzed by the Student *t* test or the Chi*-*Squared test. All analyses will be performed in SPSS software. Differences will be considered statistically significant at *P* < .05.

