**Methods::**

This study will be a prospective, single-center, double-blind randomized controlled trial. Ninety two participants diagnosed with ASBO will be randomly assigned to either the verum or the sham laser acupuncture (SLA) group in a 1:1 ratio. All participants will undergo laser acupuncture (LA) or SLA once a day on 6 acupoints (LI4, PC6, ST25, ST36, CV4 and CV12) for 6 consecutive days after enrollment. The primary outcome measure will be the success rate of conservative treatment for ASBO. Secondary outcomes will be time to oral intake and length of hospital stay. The serum levels of lipase, amylase, cortisol, motilin, ghrelin, and intestinal fatty acid binding protein (I-FABP) will also be measured before intervention, on day 4, and on the day of discharge, respectively. Data will be analyzed by Chi-Squared test or t test between 2 groups.

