## Introduction

1

Adhesive small bowel obstruction (ASBO) is one of the most common complications and is a major cause of admission after intra-abdominal surgery. The incidence of ASBO following all types of abdominal surgery is 2.4%.^[1]^ Less commonly, the adhesions may form as a result of inflammatory conditions, intraperitoneal infection or abdominal trauma.^[2]^ Definitive confirmation of ASBO is made during operative treatment. In the initial 72 hours, nonoperative management for ASBO patients is appropriate unless there are signs of peritonitis, strangulation, or bowel ischemia.^[3,4]^ Approximately 70% to 90% of patients with ASBO respond to nonoperative treatment.^[3]^ Surgery intervention for adhesions should be considered for patients with repeated ASBO or unsuccessful conservative treatment, as any delay in surgical intervention is associated with higher mortality and complication rates if nonoperative management is unsuccessful after 3 days.^[4]^ To date, the ideal management of ASBO remains disputed. Therefore, the development of a new feasible treatment to increase the likelihood of successful nonoperative treatment and reduce the recurrence of ASBO is of great clinical significance.

Laser acupuncture (LA) combines the characteristics of traditional metal-needle acupuncture and low-level laser therapy. While acupuncture has been reported to promote the recovery time of postoperative ileus in patients with colorectal cancer,^[5]^ the application of LA for ASBO is very rare, and only 1 pre-clinical study has shown low level laser therapy to be effective in preventing intra-abdominal adhesions in rabbits without compromising the strength and healing of the abdominal wall.^[6]^ We assume that conventional treatment combined with LA will be effective for reducing the need for surgery through eliminating the symptoms of ASBO. The major aim of this study is to investigate the clinical benefits and the adverse events of LA in patients with ASBO. Furthermore, we want to explore the short-term effects or changes in several serum biomarkers associated with ASBO, including serum lipase, amylase, cortisol, motilin, ghrelin, and intestinal fatty acid binding protein (I-FABP). These serum biomarkers are associated with bowel movements and injuries, as explained in the discussion section.

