### Outcome measurements

2.6

The primary outcome measurement will be the success of conservative treatment, which is defined as no need for nasogastric tube decompression or operative intervention. Secondary outcome measurements will include time to oral intake, length of hospital stay, and changes in serum amylase, lipase, cortisol, motilin, ghrelin, and I-FABP levels, which will be checked before the intervention, on the fourth day, and on the day of discharge, respectively. The reasons why participants are unable to complete the follow-up treatments or withdraw from the study, such as adverse events, suboptimal response to therapy, surgical intervention for ASBO, or refusal to receive intervention, will be recorded.

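### Changes in six serum markers would be compared by a t test without baseline adjustment, although every patient's baseline is measured, which gives up precision at no saving

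*Protocol article*

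**What the plan says.** Section 2.6 (Outcome measurements) lists among the secondary outcomes "changes in serum amylase, lipase, cortisol, motilin, ghrelin, and I-FABP levels". Samples are planned at three times: pre-treatment, day 4 and discharge. Each patient thus contributes a pre-treatment value and two later values per marker.

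Section 2.7 (Statistical analysis) covers all outcomes in one short paragraph. On presentation it states: "The data will be expressed as frequencies, percentages or mean ± standard deviation". Continuous data are thus summarised only by mean and SD. For testing, the data are to be "analyzed by the Student *t* test or the Chi*-*Squared test", and one threshold applies throughout: "Differences will be considered statistically significant at *P* < .05". The abstract repeats the choice: "Data will be analyzed by Chi-Squared test or t test between 2 groups". Neither place names a covariate model, a transformation or a rank-based test.

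The Introduction describes the purpose of the marker work in modest terms: "we want to explore the short-term effects or changes in several serum biomarkers associated with ASBO". No section gives an SD, a distribution or a baseline-to-follow-up correlation for any marker.

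**The concern.** When an outcome is measured before and after treatment, a two-group t test can be run on the change or on the follow-up value. Neither makes the best use of the baseline. The change score subtracts all of it, as if the regression of follow-up on baseline had slope 1. The follow-up comparison uses none of it, as if the slope were 0. ANCOVA estimates the slope.

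The same fact can be put in terms of chance imbalance. If the arms happen to differ at baseline by d, then with equal SDs the follow-up comparison is shifted by r·d and the change comparison by (r−1)·d. These shifts average to zero over randomisations, so they are not bias, but they add noise, and ANCOVA removes them.

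At stake is the width of the confidence intervals for six secondary outcomes in a trial whose size was not chosen with them in mind.

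**Working it through.** **Inputs.** Surgical rates 12.9% and 48.5%, power 95%, α 0.05, dropout 10% and total 92 come from section 2.4. The marker outcomes and sampling times come from section 2.6, and the tests from section 2.7. The correlation r is not in the document and is assumed to lie between 0.3 and 0.9.

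**The plan's own figure.** Pooled-variance formula for two proportions, two-sided, no continuity correction, mean rate (0.129 + 0.485)/2 = 0.307:

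n = [1.96·√(2·0.307·0.693) + 1.645·√(0.129·0.871 + 0.485·0.515)]² / 0.356² = 40.6, so 41 per arm and 82 in total. Then 82/0.9 = 91.1, rounded up to 92. The stated number reproduces. It rests on the surgical rate only, so nothing in it was planned for the markers.

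**Variance of the treatment comparison.** In units of the marker variance s², with equal variance at baseline and follow-up:

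- t test on change: 2(1−r)
- t test on the follow-up value: 1
- ANCOVA: 1−r²

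Hence ANCOVA/change = (1−r²)/[2(1−r)] = (1+r)/2, and ANCOVA/follow-up = 1−r².

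| r | change | ANCOVA | ANCOVA/change | ANCOVA/follow-up |
|---|---|---|---|---|
| 0.3 | 1.40 | 0.91 | 0.65 | 0.91 |
| 0.5 | 1.00 | 0.75 | 0.75 | 0.75 |
| 0.7 | 0.60 | 0.51 | 0.85 | 0.51 |
| 0.9 | 0.20 | 0.19 | 0.95 | 0.19 |

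**Smallest detectable difference**, 80% power, two-sided 0.05, 41 per arm, in marker SDs: (1.96 + 0.84)·√(2/41) = 0.62, multiplied by the square root of the variance above. Change versus ANCOVA: 0.73 versus 0.59 at r = 0.3, 0.62 versus 0.54 at r = 0.5, 0.48 versus 0.44 at r = 0.7.

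**Unequal variances.** If the baseline SD is k times the follow-up SD, the change-score variance is 1 + k² − 2rk. Subtracting 1−r² leaves (k−r)², which is never negative, so apart from the one degree of freedom spent on the covariate ANCOVA does not lose. At r = 0.5 the ratio ANCOVA/change is 0.75/1.75 = 0.43 for k = 1.5 and 0.75/3 = 0.25 for k = 2. Both values of k are assumptions.

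**What skew would do, if present.** A simulation with log-normal markers (41 per arm, r = 0.5 on the log scale, 2000 runs, shift of 0.5 log-SD) gave the following. All log-SDs are assumed.

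| log-SD | power, t test on raw change | power, ANCOVA on logs | type I error, t test on raw change |
|---|---|---|---|
| 0.5 | 0.60 | 0.74 | 0.051 |
| 0.8 | 0.51 | 0.72 | 0.045 |
| 1.2 | 0.35 | 0.71 | 0.041 |

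Skew would cost power; it did not inflate the error rate.

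**The case against.** The strongest reply is that nothing here is an error. A t test on change is unbiased under randomisation, already uses the baseline by subtraction, and kept its type I error close to 5% in the simulation even under strong assumed skew. The markers are exploratory by the Introduction's own account. Section 2.7 is a condensed paragraph, and covariates or transformations for laboratory outcomes are often left to an analysis plan. The gain also depends on an unknown r: against change scores it shrinks to 5% of the variance at r = 0.9.

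Most of this stands and limits the point to efficiency. What does not stand is that the document is merely silent. It names the test in two places, and nothing in it points to an adjusted analysis.

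Three stronger readings are tempting, and the document does not support them:

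- *The markers are skewed, so the t test is unsuitable.* No distribution is given. The Discussion explains what the markers mean, not how they are distributed. Right skew is plausible for concentrations but remains an assumption.
- *Baseline imbalance or a few large values make the t test misleading.* Chance imbalance is already reflected in the standard error, and neither factor was shown to produce excess false positives.
- *ANCOVA would allow fewer patients.* The total of 92 is set on the surgical rate and would not change.

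**Conclusion.** The point holds as one about precision. The planned analysis of the six marker outcomes is valid but less efficient than one that adjusts for a baseline already being collected. Relative to a t test on change, ANCOVA has 65% to 95% of the variance for r from 0.3 to 0.9. Relative to a t test on follow-up values it has 91% to 19%. These figures assume equal variances and a value of r that the document does not supply. Any further gain from a log scale depends on skew that is undocumented. The primary analysis and the sample size are untouched.

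**What to change.** State that each marker will be analysed at day 4, and likewise at discharge, by ANCOVA with treatment arm as factor and the pre-intervention value as covariate. Report the adjusted difference with its 95% CI. Keeping both times preserves the planned sampling.

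Add a conditional rule: if the blinded data, pooled over both arms and not split by the A and B labels, prove skewed, analyse log-transformed values with log baseline as covariate and report the adjusted geometric mean ratio with 95% CI. Write down the criterion for skew before the data are examined.

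The cost is wording and one model per marker and time. The baseline samples are already in the schedule, the SPSS software named in section 2.7 fits the model, and no patients, visits or assays are added. The one small downside is that, where the log scale is used, the effect measure becomes a ratio instead of a difference.

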### Sample size, blinding, and randomization

2.4

As no related studies on the effects of acupuncture or laser acupuncture for the treatment of ASBO have been published, we determined the necessary sample size based on a previous study of the effects of sesame oil on ASBO.^[7]^ The surgical rate was 12.9% in the experimental group and 48.5% in the control group. Anticipating a power of 95% (1-β = 0.95), statistical significance (α = 0.05) of 95%, and a dropout rate of 10%, a total of 92 participants will be required in this study, according to G∗power analysis.

All the participants will be informed that they will receive laser acupuncture in addition to the conventional treatment and assess the efficacy of laser acupuncture for ASBO. The laser acupuncture devices used in the LA and SLA groups will have the same appearance. The difference will be that no energy will be output during the intervention in the SLA group. The participants will be unable to recognize whether they are being treated or not because laser acupuncture involves low-intensity, non-thermal laser irradiation that it is hard to detect. Participants will be randomly allocated to either the LA or the SLA group in a 1:1 ratio using computer-generated random numbers. Randomization will be performed by an independent researcher with no involvement in the inclusion and exclusion process, treatment, or outcome assessments.

The participants, outcome assessors, and data analysts will be blinded to the allocation of interventions using labels A and B for the 2 groups until the trial is completed.

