In addition to assessing the clinical symptoms of ASBO, we will also try to assess the changes in serum biomarkers associated with bowel movements and injury. Elevated lipase and amylase levels are usually the diagnostic base of acute pancreatitis. However, elevation of lipase and amylase levels is also observed in patients with small bowel obstruction.^[16]^ Elevated serum lipase is also a risk factor for higher serum creatinine, lactate, use of intensive care, and mortality.^[17]^ We assume that elevated serum lipase and amylase levels may have poor prognosis and prolong the length of hospital stay. Cortisol is a marker not only for diagnosing hypo- or hypercortisolism but also diseases of metabolism, inflammation, the cardiovascular system, and behavior.^[18,19]^ A flatter diurnal cortisol slope is associated with poorer health and may be a marker or a mechanism for disease etiology.^[20]^ We think cortisol can be treated as a stress response to inflammation and as a tool to assess the efficacy of treatment. Ghrelin and motilin are produced in the mucosal layer of the stomach and duodenum, respectively. They are hormones that can stimulate appetite and gastrointestinal motility.^[21]^Motilin is known to contract the gastrointestinal tract through activation of smooth muscle cells, local enteric neurons, and afferent terminals of vagus nerves. Ghrelin has multiple functions; in addition to modulating gastrointestinal motility, it is also involved in glucose metabolism, lipid metabolism, and endocrine functions.^[21]^ We think motilin and ghrelin can be used for evaluating the stimulative effect of gastrointestinal motility. I-FABP is involved in the uptake and transport of long chain fatty acids from the intestinal lumen.^[22]^ I-FABP is mainly expressed in the intestinal villi, where ischemic injury first occurs, so it might be an early and useful marker for mucosal compromise or injury of the intestine as well as systemic inflammatory response syndrome.^[23]^ Thus, we will use I-FABP as a diagnostic marker for evaluating gut wall integrity loss and inflammation.

In conclusion, the results of this study are expected to indicate the efficacy of LA as a nonoperative treatment in the management of ASBO in addition to conventional treatments.

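### Length of stay and treatment success are compared without using baseline lipase, which is measured before treatment and which the protocol itself links to length of stay: a modest, nearly free gain in efficiency is passed up.

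*Protocol article*

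**What the plan says.** The Abstract gives the analysis in one sentence: "Data will be analyzed by Chi-Squared test or t test between 2 groups". The Statistical analysis section says the same: "The data will be expressed as frequencies, percentages or mean ± standard deviation and analyzed by the Student" t test or the chi-squared test. Neither place names a covariate or a model. The section on sample size, blinding and randomization describes 1:1 allocation by computer-generated random numbers and names no stratification factor.

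The Outcome measurements section makes conservative-treatment success (no nasogastric decompression and no operation) the primary outcome and length of stay a secondary one. It lists lipase and amylase among the serum markers, "which will be checked before the intervention, on the fourth day, and on the day of discharge, respectively".

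The Discussion gives the reason for measuring them: "We assume that elevated serum lipase and amylase levels may have poor prognosis and prolong the length of hospital stay". The only patient-history factor tied to surgery is in the Introduction: "Surgery intervention for adhesions should be considered for patients with repeated ASBO or unsuccessful conservative treatment".

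**The concern.** The article assumes that a baseline measurement carries information about length of stay, collects it from the patients, and then names tests that cannot use it. If the assumption is right, part of the patient-to-patient variation in length of stay could be removed from the treatment comparison at almost no cost. A t test between arms also cannot show whether lipase is related to stay, so no analysis named in the article examines the assumption.

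What is at stake is the width of an interval and some power. That matters little if the planned effect is real. It matters more if the effect is smaller, because the trial was sized on a difference of 48.5 - 12.9 = 35.6 percentage points borrowed from a study of a different treatment.

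**Working it through.** **1. The plan's own sample size.** Inputs from the sample size section: "The surgical rate was 12.9% in the experimental group and 48.5% in the control group"; power 0.95, alpha 0.05 and dropout 10%. The mean rate is (0.129 + 0.485)/2 = 0.307. The two-sided formula with pooled variance under the null gives, per arm,

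n = [1.960·√(2·0.307·0.693) + 1.645·√(0.129·0.871 + 0.485·0.515)]² / 0.356² = (1.2785 + 0.9898)² / 0.1267 = 40.6, so 41.

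The total is 82, and 82/0.9 = 91.1, so 92. This agrees with the article: "a total of 92 participants will be required in this study". The sample size and the unadjusted chi-squared test are consistent. Power with 41 evaluable per arm is Φ[(0.356·√41 - 1.2785)/0.6018] = Φ(1.663) = 95.2%.

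**2. Length of stay.** If baseline covariates explain a share R² of the within-arm variance, the standard error is multiplied by √(1 - R²), and 82 patients act like 82/(1 - R²). The article gives no R², so it is assumed over a range.

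| Assumed R² | Fall in standard error | 82 patients act like |
|---|---|---|
| 0 | 0% | 82 |
| 0.05 | 2.5% | 86 |
| 0.10 | 5.1% | 91 |
| 0.20 | 10.6% | 103 |
| 0.30 | 16.3% | 117 |

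**3. Primary outcome, surgery component only.** The article gives planning rates only for surgery, so power for the full definition, which also counts nasogastric decompression, cannot be computed. Replacing 41 by 41/(1 - R²) in the power formula of step 1 gives the table below. The 30% versus 10% scenario is illustrative. It uses the two ends of the 10% to 30% non-response implied by the Introduction, where 70% to 90% respond to nonoperative treatment.

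| Assumed R² | 48.5% vs 12.9% | 30% vs 10% |
|---|---|---|
| 0 | 95.2% | 62.3% |
| 0.05 | 96.1% | 64.6% |
| 0.10 | 96.9% | 67.0% |
| 0.20 | 98.3% | 72.2% |
| 0.30 | 99.2% | 77.9% |

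**4. Check by simulation.** 20,000 trials per scenario, 41 per arm, one normally distributed baseline score, logistic outcome with log-odds 0.7 / 1.0 / 1.4 per SD (assumed). Pearson chi-squared was compared with a linear model of the outcome on arm and score.

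- 48.5% vs 12.9%: power rises from 95-96% to 96% / 98% / 98%.
- 30% vs 10%: power rises from about 64% to 66% / 68% / 71%, and the variance of the risk difference falls by 5% / 11% / 17%.
- Score with no predictive value: variance rises by 1.0% to 1.4%, and power falls by 1 point or less.
- Type I error at 30% vs 30%: chi-squared 4.7% to 5.0%, adjusted 4.8% to 5.3%.

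**The case against.** The strongest reply is that nothing here is wrong. An unadjusted comparison is valid under 1:1 randomisation with no stated stratification, and its error rate already allows for chance imbalance. The chi-squared test is also the one that reproduces the 92. All of that stands, and it is why the chi-squared test should remain the primary test.

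A reader might infer that the protocol names factors that drive both outcomes. It does not. The lipase statement is hedged, is not tied explicitly to baseline values, and concerns prognosis and stay, not success of conservative treatment. Repeated obstruction is mentioned only as a general reason to consider surgery. The Discussion lists previous episodes as one of two usual ways to confirm the diagnosis, the other being exclusion of other causes by imaging. That does not show that previous episodes are recorded for every patient.

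A reader might also infer that the prognostic assumption is never tested. That can be said only of this article, because adjusted and exploratory analyses are often left to an analysis plan, and none is shown. The assumption is also rationale rather than a stated objective. What remains is that the article does more than stay silent: it names the tests, and for length of stay a better-informed one is available from data already being collected.

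**Conclusion.** The point holds as a low-severity efficiency improvement, clearest for length of stay. The unadjusted tests are neither an error nor a source of bias. Every gain rests on an assumed covariate strength. Over R² from 0 to 0.3 it runs from nothing to a 16% smaller standard error for length of stay. For the surgery component it is at most about 4 percentage points of power at the planning rates (95.2% to 99.2%) and at most about 16 points at 30% versus 10% (62.3% to 77.9%); the simulation gave a smaller gain there, up to about 7 points. The surgery-only figures do not give the power for the primary outcome as defined. If lipase predicts nothing, the loss is about 1% in variance.

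**What to change.** Before unblinding, prespecify the following.

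- **Length of stay:** in place of the plain t test, a linear model with arm and log baseline lipase, reporting the adjusted difference with its 95% CI. The lipase coefficient also examines the assumption made in the Discussion.
- **Primary outcome:** keep the chi-squared test. Add, as a supportive analysis, an adjusted risk difference with its 95% CI using log baseline lipase. Report the risk difference rather than an adjusted odds ratio, because logistic adjustment does not narrow the interval for the log odds ratio.
- **Repeated obstruction:** add first versus repeated episode as a second covariate only if it is recorded for all patients at baseline. Stop at two covariates: at the planning rates only about 82 × 0.307 = 25 operations are expected.

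The Abstract and the Statistical analysis section should then describe the same analyses. The cost is a few lines of analysis-plan text and one or two degrees of freedom. Lipase needs no new data collection; previous episodes may need a data field. The sample size does not change.

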### Data monitoring

2.8

No data monitoring committee (DMC) will be needed because laser acupuncture is a general practice and noninvasive intervention. Nevertheless, adverse events such as unexplained diarrhea, increased abdominal pain, and fainting during laser acupuncture treatment will be monitored during the trial period.

